### Randomization and allocation

2.9.

Trial A is a controlled observational trial without randomization and allocation.

Trial B will use a computerized central randomization system to randomize the participants in the dynamic stratified block, which is undertaken by Zhejiang Taimei Medical Technology Co. Each center will have an independent researcher log into the computerized central randomization system and generate a randomized sequence that divides eligible participants into 4 groups (WL group, CCA group, TSA group, and PSA group) in a 1:1:1:1 ratio. The researcher will have no contact with participants, acupuncturists, outcome assessors, and data statisticians. The allocation results will be stored in the central computerized randomization system password-protected.

### Blinding

2.10.

In Trial A, detectors of biological specificity of acupoints and outcome evaluators will be blinded, while participants will not be blinded. Statistical analyses will be undertaken by third-party statisticians who will be blinded to the study protocol during the data analysis phase.

In Trial B, acupuncturists will not be blinded, considering the characteristics of acupuncture therapy. Therefore, this study will be blinded on three levels: the patient, the evaluator, and the statistician. Patients will be blinded by using a single isolated treatment room for treatment and eliminating the communication between patients for comparison purposes. Outcome evaluation will be performed by evaluators who are not aware of the allocation information. Statistical analyses will be carried out by statisticians who will not have access to allocation data. Emergency unblinding will be permitted if a serious adverse event occurs and there is a need to know what intervention was used for that patient in the study.

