**Figure 1 fig1:**
[figure not shown]
Flow chart of the study process. **(A)** Flow chart of the study process of Trial A. MDD, major depressive disorder. **(B)** Flow chart of the study process of Trial B. PTG, pressure pain threshold gauge; IRT, infrared thermography; PPT, pressure pain thresholds; T_acupoint_, temperature of the acupoint; WL, waiting list; CCA, clinical common acupoints; PSA, pressure pain threshold strong response acupoints; TSA, temperature strong response acupoints; PHQ-9, the Patient Health Questionaire-9 Items; SF-36, the MOS item short form health survey.

Trial B will be a prospective, multicenter, randomized, controlled, patient-assessor-blinded study. Eligible MDD patients will be allocated randomly to waiting list (WL) group, clinical common acupoint (CCA) group, TSA group, and PSA group in a 1:1:1:1 ratio. Figure 1B shows a flow chart of the study process, and Table 1 shows the trial schedule of enrolment, treatments, and assessments. Patients will receive 6 weeks of treatment and all patients will receive basic treatment, IA for CCA, PSA and TSA, respectively. The protocol adheres to the Standards for Reporting Interventions in Clinical Trials of Acupuncture (STRICTA) (25) (Additional file 1) and the Standard Protocol Items: Recommendations for Interventional Trials (SPIRIT) statement (26) (Additional file 2). This study is prospectively registered on ClinicalTrials.gov (NO. NCT05524519).

**Table 1 tab1:** Schedule of enrolment, treatments, and assessments.

	Study period					
	Enrolment	Allocation	Baseline	Treatment period		Follow-up period
**Timepoint**	**−t** _ **1** _	**0**	**t** _ **1** _ **(week 0)**	**t** _ **2** _ **(week 3)**	**t** _ **3** _ **(week 6)**	**t** _ **4** _ **(week 10)**

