#### WL group

2.12.1.

Patients in this group will not receive IA treatment during the study period. When the study is over, they will receive 6 weeks of the same IA treatment as in the CCA group.

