#### CCA group

2.12.2.

LR3 (Taichong), PC6 (Neiguan), SP6 (Sanyinjiao) and HT7 (Shengmen) will be stimulated in this group. PC6 and HT7 will use φ0.20*1.2 mm needle, as well as LR3 and SP6 will use φ0.20*1.5 m needle. After routinely disinfecting the skin around the selected acupoints, press the needle to insert the acupoint vertically and retain it in the skin. After the intervention, the needle will be retained for 72 h with a day of rest after removal. Then the next treatment will be performed. During needle retention, participants will be instructed to press the acupoints 3–4 times a day for about 1 min each time, with the amount of stimulation as much as the patient can tolerate, at an interval of about 4 h. A total of 10 treatment sessions will be performed for 6 weeks.

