Despite this study having many strengths and highlights, it does have some limitations. First, although this study attempts to limit the influence of exogenous and endogenous factors on acupuncture point recognition by controlling the ambient temperature or humidity and requiring patients to rest enough before doing the test, there may be some errors in the two detection techniques. In addition, to minimize measurement errors, we will provide uniform training for the testing staff before the formal test. Second, due to time and financial constraints, large sample size and long-term follow-up will be not possible, so the sample size of this study will be small with a short follow-up period. However, the results of this study may still provide evidence for the feasibility of this trial design and provide basic data for future full-scale trials. We hope to expand the sample size and extend the follow-up period in the future to assess the long-term treatment effects of snap for MDD. Third, the nature of the IA treatment method makes it difficult to blind the IA operators in our study. To minimize the subjective influence, our study outcome assessment and statistical analysis will be performed by a third party who is unaware of the subgroup. Fourth, we only set up a medicine group without setup a sham acupuncture control group. Although we do not set up a sham IA group, thereby failing to exclude a possible placebo effect of IA. However, we believe that if there is a placebo effect, it is part of the IA effect.

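### Trial B is called patient-blinded without exception, but patients can be masked only to the acupoint set among the three IA arms; every IA-versus-waiting-list contrast on PHQ-9 and SF-36 is open-label

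*Protocol article*

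**What the plan says.** All places are in the protocol article.

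- **Label.** Section 2.1: "Trial B will be a prospective, multicenter, randomized, controlled, patient-assessor-blinded study". Section 2.10: "Therefore, this study will be blinded on three levels: the patient, the evaluator, and the statistician". Neither limits the claim to particular arms.
- **How patients are masked.** Section 2.10: "Patients will be blinded by using a single isolated treatment room for treatment and eliminating the communication between patients for comparison purposes". No other means is given.
- **WL arm.** Section 2.12.1: "Patients in this group will not receive IA treatment during the study period". It continues: "When the study is over, they will receive 6 weeks of the same IA treatment as in the CCA group".
- **IA arms.** Under section 2.12.2 each needle stays in the skin for 72 hours, and "During needle retention, participants will be instructed to press the acupoints 3–4 times a day for about 1 min each time". Sections 2.12.3 and 2.12.4 carry this procedure over to the PSA and TSA arms.
- **Outcomes.** Section 2.13.2 makes change in PHQ-9 primary and change in SF-36 secondary. Each PHQ-9 item is scored by how often the patient has had the symptom.
- **Aims.** Section 2.1 has two: the therapeutic effect and safety of IA, and whether strong response acupoints are superior to common ones.
- **Limitations.** The Discussion names the IA operators as hard to blind. It concedes that there is no sham arm and that a placebo effect is not excluded, then adds: "we believe that if there is a placebo effect, it is part of the IA effect".

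**The concern.** Isolated rooms and no contact between patients can conceal which points are used. They cannot conceal whether needles are used at all. For the WL arm, the declared patient blinding is therefore a property that the design does not have.

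This matters because of the outcome. Blinding the evaluator does little for a score that consists of the patient's own answers when the patient knows the allocation. Hope among those needled, or disappointment among those told to wait, enters PHQ-9 and SF-36 directly.

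WL is the only arm without IA, so the first aim rests on exactly these contrasts. With the label left as it stands, a reader could take an IA-versus-WL difference as efficacy shown under patient blinding.

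**Working it through.** The plan states no effect size, SD or power for Trial B (section 2.5), so there is no figure to reproduce. The check is mainly a comparison of sections.

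**Step 1: what each patient can know.**

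| Arm | IA during the study | Patient knows IA or no IA? | Patient can be masked to acupoint set? |
|---|---|---|---|
| WL | none; offered afterwards | yes | not applicable |
| CCA | retained needles, pressed daily | yes | yes |
| TSA | same procedure | yes | yes |
| PSA | same procedure | yes | yes |

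**Step 2: which contrasts are masked.** Four arms give 4 × 3 / 2 = 6 possible pairs. The article does not prespecify six pairwise tests; the count only sorts the contrasts.

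- Open (3): CCA vs WL, TSA vs WL, PSA vs WL.
- Patient masking possible (3): PSA vs CCA, TSA vs CCA, PSA vs TSA.

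**Step 3: which aim is affected.** The effect of IA needs a comparator without IA, so it rests on the three open contrasts. Strong response versus common acupoints rests on PSA vs CCA and TSA vs CCA, which are masked.

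**Step 4: illustration of what is at stake.** Inputs from the article: 120 patients at 1:1:1:1, so 120 / 4 = 30 per arm, and a significance level of 0.05. Assumptions: a two-sided test, no specific needling effect, and an expectation-only shift of *d* SD in PHQ-9.

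P(significant) = 1 − Φ(1.96 − d/SE) + Φ(−1.96 − d/SE), with SE in SD units:

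- one IA arm vs WL: SE = √(1/30 + 1/30) = 0.258
- three IA arms pooled vs WL: SE = √(1/30 + 1/90) = 0.211

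| Assumed shift d (SD) | One IA arm vs WL | Pooled IA vs WL |
|---|---|---|
| 0 | 0.050 | 0.050 |
| 0.1 | 0.067 | 0.076 |
| 0.2 | 0.121 | 0.158 |
| 0.3 | 0.213 | 0.296 |
| 0.4 | 0.341 | 0.475 |
| 0.5 | 0.491 | 0.660 |

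Example at d = 0.2: 0.2 / 0.258 = 0.775, so 1 − Φ(1.185) + Φ(−2.735) = 0.118 + 0.003 = 0.121. If the PHQ-9 SD were 5 (also an assumption), 0.2 SD would be 1 point and 0.4 SD 2 points.

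**The case against.** **The consequence is already disclosed.** The Discussion says that there is no sham arm and that placebo is not excluded, and it describes the control as a medication group. A careful reader is therefore warned about IA versus WL. This is fair as far as it goes. But the limitation on blinding names only the operators, nothing says that WL patients are unblinded, and the label in sections 2.1 and 2.10 stands. Counting placebo as part of the IA effect is an interpretive choice. It is defensible for an open add-on question, but not alongside a claim of patient blinding.

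**The main superiority question is untouched.** This stands. The comparison of strong response with common acupoints keeps its patient masking, and the point should not be stretched to the whole trial.

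**Stronger readings that a reader might infer, and why the documents do not support them:**

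- *Evaluator blinding also fails.* Needles in for 72 hours plus one day of rest make a 4-day cycle. With session 1 on day 0, session 6 spans days 20 to 23 and covers a day-21 visit. But section 2.12.2 fixes no start day; it says only "A total of 10 treatment sessions will be performed for 6 weeks". Ten cycles take 40 of 42 days, which leaves slack. With a start on day 2, session 5 ends on day 21 and session 6 begins on day 22. Only the questionnaires are due at week 3, and nothing says that those evaluators see the skin. On a day-0 start the last needles come out on day 39, three days before week 6, and no section says that marks remain. Evaluator unblinding is possible, not shown.
- *The probabilities are the trial's false-positive rates.* They are not. They show the power of a simple two-arm comparison to detect an assumed shift, and section 2.16 plans repeated-measures ANOVA.
- *Efficacy should rest on the masked contrasts alone.* All arms in those contrasts receive IA, so the first aim would go untested.

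**Conclusion.** The blinding statement is wrong as written. Sections 2.1 and 2.10 claim patient blinding for all of Trial B, while sections 2.12.1 and 2.12.2 make it impossible between WL and any IA arm. All three IA-versus-WL contrasts on PHQ-9 and SF-36 are open-label and cannot separate needling from expectation; the three contrasts among IA arms can keep patient masking.

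The conclusion follows from the article's own description of the arms and needs no numerical assumption. It does take PHQ-9 and SF-36 as resting on the patient's answers. The article does not say that the forms are self-completed, but the point holds equally if an evaluator reads out the items. How large an expectation effect might be cannot be learned from the document, and the table is an illustration only.

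**What to change.** 1. **Sections 2.1 and 2.10.** State that patients are masked to the acupoint set among the CCA, TSA and PSA arms only, and that the WL arm is open. The statements on evaluators and statisticians need no change on this account.
2. **Interpretation of IA versus WL.** Describe it as the effect of adding open-label IA to basic treatment, expectation included. It remains the contrast that addresses the first aim.
3. **Strong response versus common acupoints.** Keep PSA vs CCA and TSA vs CCA as the masked comparisons, and say so. PSA vs TSA is masked as well.
4. **Discussion.** Keep the sentence on placebo but qualify it: any placebo effect is included in the IA-versus-WL difference because that contrast is open. Name WL patients, beside the operators, as unblinded.

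The cost is wording; arms, visits and sample size stay as they are. The downside is that the IA-versus-WL claim becomes weaker.

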### Biological specificity detection of acupoints (Trial A)

2.11.

To minimize the interference effects caused by confounding circumstances, all examinations will be performed almost simultaneously in the morning. A controlled condition experimental room will be adopted, with a temperature of (26 ± 1)°C, relative humidity of 40–50%, no direct sunlight and abnormal radiant source, no significant air convection, and good sound insulation. All subjects will be prohibited from drinking coffee, tea, alcohol, smoking cigarettes, or eating spicy foods on the examination day. Food and exercise will be also not allowed for at least 1 hour before the trial. After entering the experimental room, subjects will be needed to expose the test site and relax for 30 min before the formal examination to adjust to the surrounding. Throughout the exam, subjects will be asked to remain silent, breathe naturally, and relax. Before the examination, basic physiological parameters including heart rate, blood pressure, and body temperature will be taken from the subject. Based on the results of our group’s data mining of the literature related to acupuncture for MDD, 39 acupoints closely related to MDD will be selected as test sites. The IRT test will be not done on the acupoints where the hair is dense. According to the National Standard for the Name and Positioning of Acupuncture Points (GB/T 12346–2006). The anatomical locations of the acupoints are displayed in Table 3 and Figure 2.

**Table 3 tab3:** Location and indication of MDD-related acupoints.

Acupoints	Location
Head, face, and neck	
Baihui (GV20)	On the head, 5.0 cun directly above the midpoint of the anterior hairline. Or, at the midpoint of the line connecting the apexes of the two auricles.
Yintang (GV29)	At the forehead, at the midpoint between the two medial ends of the eyebrow.
Sishencong (EX-HN1)	At the vertex of the head, a group of four points, 1.0 cun, respectively, anterior, posterior and lateral to Baihui (GV 20).
Shenting (GV24)	On the head, 0.5 cun directly above the midpoint of the anterior hairline.
Shuigou (GV26)	On the face, at the junction of the superior 1/3 and middle 1/3 of the philtrum.
Taiyang (EX-HN5)	In the region of the temples, in the depression about one finger-breadth posterior to the midpoint between the lateral end of the eyebrow and the outer canthus.
Fengchi (GB20)	On the nape, below the occiput, at the level of Fengfu (GV 16), in the depression between the upper portion of m. sternocleidomastoideus and m. trapezius.
Upper limbs	
Quchi (LI11)	With the elbow flexed, the point is on the lateral end of the transverse cubital crease, at midpoint between Chize (LU 5) and the lateral epicondyle of the humerus.
Hegu (LI4)	On the dorsum of the hand, between the 1st and 2nd metacarpal bones, in the middle of the 2nd metacarpal bone on the radial side.
Pianli (LI6)	With the elbow flexed, the point is on the dorsal radial side of the forearm, on the line connecting Yangxi (LI 5) and Quchi (LI 11), 3 cun above the wrist crease
Yanggu (SI5)	On the ulnar aspect of the wrist, in the depression between the styloid process of the ulna and the triquetral bone.
Zhizheng (SI7)	On the dorsal ulnar aspect of the forearm, 5 cun above the transverse crease of the wrist, on the line connecting Yanggu (SI 5) and Xiaohai (SI 8).
Chize (LU5)	On the cubital crease, on the radial side of the tendon m. biceps brachii.
Yuji (LU10)	In the depression behind the thenar eminence of the thumb, about the midpoint of the palmar side of the thumb, on the junction of the red and white skin.
Neiguan (PC6)	On the palmar aspect of the forearm, 2 cun above the transverse crease of the wrist, on the line connecting Quze (PC 3) and Daling (PC 7), between the tendons of m. palmaris longus and m. flexor carpi radialis.
Shaohai (HT3)	When the elbow is flexed, the point is at the midpoint of the line connecting the medial end of the transverse cubital crease and the medial epicondyle of the humerus.
Tongli (HT5)	On the palmar aspect of the forearm, the point is on the radial side of the tendon m. flexor carpi ulnaris, 1.0 cun above the transverse crease of the wrist.
Shenmen (HT7)	On the wrist, at the ulnar end of the transverse crease of the writs, in the depression on the radial side of the tendon m. flexor carpi ulnaris.
Lower limbs	
Zusanli (ST36)	On the anterior aspect of the lower leg, 3 cun below Dubi (ST 35), one finger-breadth (middle finger) from the anterior crest of the tibia.
Fenglong (ST40)	On the anterior aspect of the lower leg, 8 cun superior to the external malleolus, lateral to Tiaokou (ST 38), two finger-breadth (middle finger) from the anterior crest of the tibia.
Jiexi (ST41)	At the junction of the dorsum of the foot and the lower leg. in the depression at the midpoint of the transverse crease of the ankle between the tendons m. extensor hallucis longus and digitorum longus.
Yanglingquan (GB34)	On the lateral aspect of the lower leg, in the depression anterior and inferior to the head of the fibula.
Waiqiu (GB36)	On the lateral aspect of the lower leg, 7 cun above the tip of the external malleolus, on the anterior border of the fibula, at the level of Yangjiao (GB 35).
Qiuxu (GB40)	On the foot, anterior and inferior to the external malleolus, in the depression on the lateral side of the tendon of m. extensor digitorum longus.
Shenmai (BL62)	In the depression directly below the external malleolus.
Sanyinjiao (SP6)	On the medial aspect of the lower leg, 3 cun above the medial malleolus, on the posterior border of the medial aspect of the tibia.
Yinlingquan (SP9)	On the medial aspect of the lower leg, in the depression of the lower border of the medial condyle of the tibia.
Taichong (LR3)	On the dorsum of the foot, in the depression proximal to the 1st metatarsal space.
Taixi (KI3)	On the medial aspect of the foot, posterior to the medial malleolus, in the depression between the tip of the medial malleolus and tendo calcaneus.
Zhaohai (KI6)	On the medial aspect of the foot, in the depression below the tip of the medial malleolus.
Xingjian (LR2)	On the dorsum of the foot, proximal to the margin of the web between the 1st and 2nd toes, at the junction of the red and white skin.
Back and lumbar	
Dazhui (GV14)	On the posterior median line, in the depression below the spinous process of the 7th cervical vertebra.
Xinshu (BL15)	On the back, 1.5 cun lateral to the lower border of the spinous process of the 5th thoracic vertebra.
Ganshu (BL18)	On the back, 1.5 cun lateral to the lower border of the spinous process of the 9th thoracic vertebra.
Pishu (BL20)	On the back, 1.5 cun lateral to the lower border of the spinous process of the 11th thoracic vertebra.
Shenshu (BL23)	On the back, 1.5 cun lateral to the lower border of the spinous process of the 2nd lumbar vertebra.
Chest and abdomen	
Guanyuan (CV4)	On the anterior median line of the lower abdomen, 3 cun below the umbilicus.
Zhongwan (CV12)	On the anterior median line of the upper abdomen, 4.0 cun above the umbilicus.
Qimen (LR14)	On the chest, directly below the nipple, in the 6th intercostal space, 4 cun lateral to the anterior midline.

MDD, Major depressive disorder.

**Figure 2 fig2:**
[figure not shown]
The anatomical locations of the acupoints.

#### PTG

2.11.1.

The FDX25 handheld pressure pain gauge will be used to detect the PPT of acupoints. The probe will be positioned vertically on the measurement acupoint, pressure will be applied slowly and steadily, and pressure will be withdrawn as soon as the patient feels pain. The PPT of the acupoint will be displayed on the gauge. Repeat the procedure 3 times at 5 min intervals.

The data will be entered into Excel. The basic PPT of the acupoint will be determined as the average of the 3 times PPT values. The top 4 acupoints most associated with MDD in PTG test will be selected as PSA by logistic regression analysis.

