### Aim, design and setting of the study

2.1.

The overarching goal of the trial is to evaluate the therapeutic effect and safety of IA for MDD and demonstrate whether stimulating strong response acupoints is superior to clinical common acupoints in the treatment of MDD.

This study will be divided into two parts (Trial A and Trial B).

Trial A will adopt a controlled, assessor-blinded design, in which eligible MDD patients and HC participants will be assessed at acupoints using PTG and IRT. Figure 1A shows a flow chart of the study process. The potentially superior acupoints for the treatment of MDD will be chosen independently based on the outcomes of the PTG and IRT tests. After statistical analysis, four pressure pain threshold strong response acupoints (PSA) and four temperature strong response acupoints (TSA) will be selected, respectively. These two groups of acupoints will be used in corresponding arms in the trial B.

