### Study participants

2.3.

To minimize the potential impact of gender and age on the biological characteristics of the 2 kinds of acupoint mentioned previously, this study will employ a gender- and age-matching strategy in the trial A, which involved the selection of HC participants and MDD patients.

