### Sample size estimation

2.5.

Since there are no relevant references for detecting the biological characteristics of MDD-related acupoints, we referred to the literature on acupoint detection (23, 27) and planned to recruit 30 MDD patients and 30 HC participants in trial A according to the principle of minimum sample size.

In Trial B, we did not estimate the sample size based on power calculations because there was no reference to indicate how effective the use of IA for MDD might be based on changes in the biological specificity of acupoints. To meet the need for minimum sample size, we instead recruited 120 participants.

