#### IRT

2.11.2.

An infrared thermography camera (NEC InfRec R450, Avio Infrared Technologies Co., Ltd., Tokyo) with measuring wavelengths of 8–14 um, a temperature resolution of 0.025°C, and a resolution of 640 × 480 pixels, will be used to record thermal images to assess the heat radiation properties of the acupuncture points. By adjusting the height and angle of the machine, the subject’s measured sites will be on the camera screen distinctly. One researcher will use a cotton swab to mark the tested acupoints, and another researcher will operate the electronic cursor of the camera to the corresponding acupoint localization and record the coordinates. Turn off the lights and focus on the camera, then start recording the thermal images. Using the interval shooting mode, 1 thermal image will be taken automatically every 10s, and 1 min continuously, a total of 6 thermal images will be taken. The subject will be instructed to remain still during the measurement.

The InfRec Analyzer NS9500 (Avio Infrared Technologies Co., Ltd., Tokyo) will analyze all thermal images, displaying different temperatures in different colors and selecting the region where the temperature will be measured. The temperature data collecting parameter of the region of interest (ROI) will be set up as a circular area within a radius of 5 mm from the acupoint, which will be the same size as an acupoint in this study. TROI will be used as the average temperature of the ROI in 1 thermal image. The average TROI in the 6 thermal images will be calculated as the temperature of the acupoint (T_acupoint_). The top 4 acupoints most associated with MDD in IRT test will be selected as TSA by logistic regression analysis.

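### Trial A always names four strong-response points per modality, with no condition on the evidence, and two Trial B arms inherit the label

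*Protocol article*

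**What the plan says.** Section 2.1 fixes the number of points in advance: "After statistical analysis, four pressure pain threshold strong response acupoints (PSA) and four temperature strong response acupoints (TSA) will be selected, respectively". It then assigns these sets to the corresponding arms of Trial B.

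Section 2.11.1 gives the rule for pressure pain threshold (PPT): "The top 4 acupoints most associated with MDD in PTG test will be selected as PSA by logistic regression analysis". Section 2.11.2 gives the rule for temperature: "The top 4 acupoints most associated with MDD in IRT test will be selected as TSA by logistic regression analysis". Section 2.16 adds only that logistic regression will be used for the screening, and sets a general significance level of 0.05 without tying it to the selection.

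On candidates, section 2.11 says "39 acupoints closely related to MDD will be selected as test sites", with the restriction "The IRT test will be not done on the acupoints where the hair is dense". On size, section 2.5 says the investigators "planned to recruit 30 MDD patients and 30 HC participants in trial A according to the principle of minimum sample size". On design, section 2.3 says "this study will employ a gender- and age-matching strategy in the trial A".

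The article does not say whether all points enter one model or each is modelled alone, by what measure points are ranked, how the matching enters, or what happens if no point differs.

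**The concern.** The trial's hypothesis (sections 1 and 3) is that needling acupoints with marked biological specificity works better than needling commonly used ones. The PSA and TSA arms are meant to embody that property. The rule takes the four highest-ranked points regardless of how weak the association is, so the strong-response label is guaranteed before any data are seen. With many candidates and few people, the highest-ranked points will look different from controls even when nothing is there.

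At stake is what a Trial B result means. If the chosen points are largely noise, a difference between PSA or TSA and the common-acupoint arm, or its absence, says little about biological specificity. Trial B's own analysis cannot repair that afterwards.

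**Working it through.** **Inputs**
- People: 30 patients and 30 controls, n = 60 (section 2.5). No effect size, SD or power is given, so this figure cannot be reproduced.
- Candidates: 39 (section 2.11). Recount of Table 3: 7 + 11 + 13 + 5 + 3 = 39.
- Candidates for temperature: fewer than 39, number not given. Table 3 places GV20, EX-HN1, GV24 and GB20 on the scalp or nape. Dropping all four leaves 39 − 4 = 35, so 35–38 is taken as an assumption.
- Significance level: 0.05 (section 2.16).
- Between-point correlation: not in the article; 0, 0.3 and 0.6 are assumed.

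**Step 1: the rule when no point differs.** 4,000 simulated data sets of 30 v 30, each point tested alone. A two-sample t test stands in for single-point logistic regression, with |d| = |t| × √(2/30).

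| Points | Correlation | P(at least one p<0.05) | P(four or more p<0.05) | Mean abs. d of top four |
|---|---|---|---|---|
| 39 | 0 | 0.86 | 0.13 | 0.53 |
| 39 | 0.3 | 0.76 | 0.16 | 0.51 |
| 39 | 0.6 | 0.48 | 0.16 | 0.46 |
| 35 | 0 | 0.83 | 0.10 | 0.52 |
| 35 | 0.3 | 0.70 | 0.13 | 0.49 |
| 35 | 0.6 | 0.45 | 0.14 | 0.44 |

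Check for 39 independent points: 1 − 0.95^39 = 0.865, and the expected number with p<0.05 is 39 × 0.05 = 1.95. Four points are named in every run.

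**Step 2: the rule when four points truly differ** (assumed d at those four, zero elsewhere; single-point ranking, 39 points, correlation 0 to 0.6). The mean number of true points among the four chosen is 1.1–1.4 for d = 0.3, 2.0–2.5 for d = 0.5 and 3.2–3.5 for d = 0.8. Random choice would give 4 × 4/39 = 0.41. By the normal approximation, single-point power at d = 0.5 is Φ(0.5/√(2/30) − 1.96) = 0.49. The d needed for 80% power is (1.960 + 0.842) × √(2/30) = 0.72.

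**Step 3: if all points enter one unpenalised model.** There are 30/39 = 0.77 cases per predictor. With no association, Cover's formula for p predictors plus an intercept gives P(perfect separation) = Σ_{k=0..p} C(59, k) / 2^59.

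| p | 39 | 38 | 37 | 36 | 35 | 20 | 10 |
|---|---|---|---|---|---|---|---|
| P | 0.996 | 0.991 | 0.982 | 0.966 | 0.941 | 0.009 | about 0 |

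Linear-programming checks on simulated 30 v 30 null data (600 runs each) gave 0.997–0.998 for 39 points and about 0.93 for 35. Under separation no finite maximum-likelihood estimate exists, so a ranking by coefficient or Wald p value has no meaning. The table also shows that the problem vanishes when few predictors enter.

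**Step 4: matching.** Section 2.3 commits to matching; sections 2.11.1, 2.11.2 and 2.16 describe no analysis that uses it. Conditioning alone would not rescue a joint model: 30 pair differences with 35–39 predictors are separated with probability 1. Conditioning helps only with single-point or penalised models.

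**The case against.** The strongest reply is that the article never says the model is joint. Screening one point at a time fits its wording at least as well, and separation is then generally not an issue. Model form is also something an article may leave to its analysis plan. That stands: the 0.996 figure is conditional, and a reader who infers that the planned model is almost surely separated goes beyond the text.

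Two further inferences are unsupported. A reader might suppose that points will be ranked by raw odds ratios, which depend on each site's spread; no ranking measure is named. A reader might also say that the analysis ignores the matching; the article is silent on how matching is handled and on whether it is by pair or by frequency.

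It can also be said that Trial B is randomised, that section 3 presents it as validating a way of selecting points, that the selected points are described as only potentially superior, and that the limitations admit a small sample. Noise in the ranking then mainly dilutes the contrast, and Step 2 shows the rule doing better than chance when real differences exist. This is fair, and it limits the consequence.

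It does not answer the central point. The number four, the label and the absence of any evidence condition are stated in the article itself, and they hold under every model form.

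**Conclusion.** The point holds for the forced selection and the label. With no true difference, four or more of 39 points would reach p<0.05 only about 13–16% of the time (10–14% with 35 points), yet four are always called strong-response, with a mean apparent |d| of about 0.46–0.53 (0.44–0.52 with 35). These figures rest on single-point testing and assumed correlations of 0–0.6.

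Separation is a conditional warning: probability about 0.996 for one unpenalised model with 39 points, and 0.94–0.99 if 35–38 remain for temperature. The matching point is that the described analysis does not reflect it.

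It would be tempting to conclude that Trial B becomes uninterpretable. The documents do not support that. Randomisation keeps PSA or TSA versus the common-acupoint arm a valid comparison of the sets actually used, and of the procedure that chose them. What is lost, if the chosen points are noise, is the attribution of any result to biological specificity.

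**What to change.** In sections 2.11.1, 2.11.2 and 2.16:
- Fit one model per acupoint, with PPT or temperature entered per SD. Use conditional logistic regression if controls are matched in pairs, or adjust for age and sex if matching is by frequency, and say which applies.
- Rank by absolute standardised log-odds ratio. Do not use an unpenalised joint model; if a joint model is wanted, use ridge or elastic net.
- Before using the strong-response label, run one global permutation test per modality that respects the matching (labels swapped within pairs if paired), and report bootstrap selection frequencies for each point.
- If the test is not passed, call the set the highest-ranked points and do not attribute the Trial B result to biological specificity. Four points can still be carried forward, so the arms are unaffected.

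The cost is a little more programming, possibly outside SPSS, with no extra participants or measurements. The downside is that the label may have to be given up. With single-point power of 0.49 at d = 0.5, failing the test would not show that no point differs.
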